## Abstract

**Background:**

The overdose epidemic in the United States has continued to worsen despite substantial efforts to mitigate its harms. The opioid antagonist naloxone has been identified as a key means of reducing the prevalence of fatal overdoses. An important evidence-based approach to optimizing naloxone’s impact is to seed it throughout the community, because bystanders are often able to reverse overdoses more quickly than first responders and sometimes are the only possible means of overdose reversal. As part of a multipronged approach to distributing naloxone nationwide, community pharmacies have been identified as ideal venues for naloxone dispensing, especially under standing orders. However, dispensing rates remain surprisingly low, and there is a need to understand how best to engage community pharmacies in naloxone-based harm reduction services.

**Objective:**

The objective of this trial is to determine whether a tailored, pragmatic pharmacy intervention (PharmNet) results in greater naloxone dispensing relative to baseline (the prior 3 months) compared to a control condition. This pilot trial is intended to determine whether it is appropriate to invest the substantial resources that would be required to conduct a full-scale, randomized controlled study of PharmNet.

**Methods:**

We will conduct a 3-month randomized controlled pilot trial consisting of 2 parallel groups with a 4:3 allocation ratio. A group of 7 independent pharmacies from rural areas in Indiana will be randomly assigned to either the PharmNet intervention arm (n=4) or the control arm (n=3). The primary outcome will be overall naloxone dispensing (both at cost and free), and secondary outcomes will include the distribution of referral cards and multiple variables at the level of individual staff members. Dispensing data will be collected for the 3 months prior to the intervention and the 3 months of the intervention, and all other data will be collected using a pretest-posttest design. The primary analysis will be a generalized linear mixed model with a Poisson distribution with fixed effects for group, time, and their interaction and a random effect for pharmacy ID to account for repeated measures within pharmacies.

**Results:**

This study was approved by the Indiana University institutional review board in 2 phases (August 2, 2021, and April 26, 2022) and was funded by the Indiana University Grand Challenge: Responding to the Addictions Crisis.

**Conclusions:**

If this study produces evidence that the PharmNet intervention results in increased naloxone dispensing relative to control pharmacies, it will be both appropriate and important to study it in a large, full-scale randomized controlled trial.

**International Registered Report Identifier (IRRID):**

PRR1-10.2196/42373

## Introduction

### Overdose Deaths in the United States

The prevalence of overdose deaths in the United States has continued to increase in recent years, eclipsing 100,000 such deaths (year over year) for the first time in June 2021 [1]. The majority of such deaths involve opioids; more specifically, in the current wave of the overdose epidemic, they involve heroin, fentanyl, and its analogues—the latter 2 of which are often introduced as adulterants in other substances (eg, stimulants) [1,2]. Largely related to such deaths, the United States renewed a declaration of an opioid public health emergency in April 2022 [3]. In the state of Indiana, where the proposed study will take place, provisional data indicated 2554 fatal drug overdoses in 2021, of which more than 78% involved opioids [4].

Naloxone, an opioid antagonist, has become a key component of the US response to the crisis [5], as it can reverse the effects of an overdose and prevent death [6,7]. However, the effectiveness of naloxone depends on the time it is administered relative to the time of the overdose. Deaths from heroin overdose can occur relatively quickly [8], and even when they do not, they typically happen within 1 to 3 hours of overdose [9]. Deaths from fentanyl overdose may occur even more rapidly [10], potentially due to differences in pharmacology between fentanyl and other opioids [11,12]. Unfortunately, individuals who witness an overdose may be hesitant to contact first responders [13,14], and even when they do, there is still variable lag time between the call for assistance and the arrival of assistance due to a variety of factors (eg, distance from the dispatch site to the overdose location). In some cases involving fentanyl, death may occur before first responders arrive [10]. Thus, there is an ongoing need to better ensure that naloxone is readily available to prevent overdose deaths.

In 2018, the US Surgeon General recommended that all people in the United States be prepared by having naloxone on hand to help in case of an overdose [15]. That recommendation followed, and has been followed by, evidence that overdose education and layperson and/or bystander administration of naloxone are safe and effective approaches to reducing the likelihood of opioid overdose fatality [16-19]. Similar to many states, Indiana has adopted laws to facilitate community overdose reduction using naloxone [20], including “good Samaritan” laws [21]. Although the means by which people obtain naloxone and other information related to harm reduction remain diverse, our focus in this proposed study is on community pharmacies.

### Role of Community Pharmacies in Harm Reduction

Community pharmacies are well positioned to provide harm reduction services to all community members, along with more targeted services to individuals at risk of overdose. Almost 9 in 10 Americans live within 5 miles of a community pharmacy [22], meaning pharmacists are among the most accessible health care professionals [23]. Among some populations (eg, Medicare beneficiaries), it has been shown that pharmacists interact with patients more often than their primary care physicians [24].

In addition to their accessibility, pharmacies increasingly are perceived as effective venues for both clinical and nonclinical harm reduction owing to pharmacists’ expertise in fields such as medication management and pharmaceutical education [25,26]. A study of Arizona pharmacists found that even when uncomfortable with most forms of harm reduction, pharmacists were generally comfortable with dispensing naloxone [27]. In Indiana, qualitative data from managing pharmacists found conceptual support for harm reduction but, simultaneously, concerns about systemic barriers to implementation, including a lack of time for interventions as well as concerns about role clarity and patients’ expectations of what should happen in a pharmacy [28]. Similar patterns of support and concern were raised in a more recent study of key informants (including pharmacists) in Connecticut, Kentucky, and Wisconsin, reflecting willingness to discuss naloxone with patients but barriers related to role clarity as well as the financial cost of naloxone [29].

Thus, despite comfort and willingness to support harm reduction and treatment, as well as faciliatory state laws (eg, standing orders permitting naloxone dispensing without a patient-specific prescription), a recent systematic review found that naloxone was stocked on average in 62.8% of community pharmacies, with both the likelihood of stocking and willingness to dispense without a prescription significantly lower in independent pharmacies than in chain pharmacies [30]. That finding was echoed by a contemporary analysis of naloxone nasal spray stocking in 11 US states, which reported a similar rate (69.5%) and a significantly lower likelihood of stocking among independent pharmacies [31].

### Our Approach to Harm Reduction Intervention in Pharmacy: the Proposed Study

The proposed study will be a pilot randomized controlled assessment of the effectiveness of PharmNet, a harm reduction intervention for community pharmacies focused on naloxone distribution, awareness building, and referral. As described in the write-up of our single-site pilot study, “the intention was to study procedures that have as minimal an impact as possible on pharmacy costs and operational functioning while maximally facilitating harm reduction from opioid overdose—in other words, to find an optimal intersection point of those concerns” [32]. In brief, the intervention includes [32]:

Building awareness of naloxone availability at the site among patients (eg, the use of yard signs and scrolling messages on television screens);Supporting awareness among pharmacists and pharmacy technicians about proactively offering naloxone (eg, customized post-it notes);Facilitating service provision by conducting a priori negotiations and establishing written agreements with local nonprofits to facilitate a pipeline of no-cost naloxone for the pharmacy;Emphasizing bidirectional naloxone provision (eg, pharmacist- and pharmacy technician–initiated offers in addition to patient-initiated requests); andFacilitating referral by providing a physical, durable, and curated list of community resources that can be used by pharmacists, handed to patients, and placed into pharmaceutical bags.

Our previous single-site pilot study found that during the intervention, compared to the mean of the 3 months of practice prior to the intervention, the monthly rate of naloxone sold had a relative increase of 34.4% (+3.33 doses/month), and the overall naloxone dispensing rate through *any* mechanism (eg, including newly added no-cost dispensing) increased 96.48% (+9.33 doses/month) [32].

Although the intervention is conceptually simple, the decisions made in its development involved highly intentional design. Changes to the program were rooted in the Consolidated Framework for Implementation Research because it allows for considerations to be addressed within complex settings, such as pharmacies [33]. The PharmNet team conducted numerous information gathering, feasibility, and methodological studies in preparation for the single-site pilot to obtain increasingly specific information and context, including both quantitative and qualitative work. Much of this work was conducted in conjunction with academic and community-based pharmacists and involved data collection from hundreds of managing pharmacists in 2 states [27,28,34-42]. The single-site pilot itself was informed by independent community pharmacists at a more granular level to maximize likely acceptability and feasibility [32].

### Study Objectives and Hypotheses

Our study will be designed to facilitate an improved understanding of whether it is reasonable to believe that the PharmNet intervention causes increased dispensing of naloxone by randomizing independent pharmacies that are part of the same small pharmacy chain to either (1) the PharmNet intervention or (2) operations as usual (control). It will also explore multiple secondary outcomes and questions.

Hypothesis 1: Monthly naloxone dispensing (combined sales and no-cost distribution) will be significantly increased in the pharmacies implementing PharmNet compared to those in the control arm.Other preregistered analyses: This study will observe the volume of PharmNet referral cards distributed by the intervention sites. It will also collect several measures from staff members (pharmacists and technicians) to provide a broader understanding of the intervention, such as staff members’ comfort with multiple harm reduction practices, stigmatizing beliefs about people who use drugs, and perceptions of intervention acceptability.

## Methods

### Ethics Approval

This study will comply with all ethical regulations as outlined and approved by the Indiana University institutional review board (IRB; 12339 and 13956). The pharmacy employee data collection for this study was approved with a designation of “exempt” from the Indiana University IRB (13956).

### Confidentiality

Pharmacy employees’ responses will be linked to their provided email addresses in a survey platform (QualtricsXM) that is approved by Indiana University for “critical data,” the highest security designation. Survey responses will not be shared outside of the research team, and data will only be reported and analyzed in aggregate.

No other identifiable data will be obtained by the research team (eg, naloxone-dispensing data will be obtained only in aggregate for the prespecified time periods).

### Design

#### Trial Design

The PharmNet pilot trial will be a cluster randomized trial consisting of 2 parallel groups and a 4:3 allocation ratio of intervention to control. The independent pharmacy organization participating in the project consists of 8 pharmacies, of which 1 was the pilot and feasibility test site [32]. The remaining 7 pharmacies will be allocated using a web-based random sequence generator (conducted by author [name]), such that 4 pharmacies will be selected to implement PharmNet, and 3 pharmacies will serve as controls (pharmacy practice as normal). The workflow for the study is provided in Figure 1**.**

This study will utilize partial blinding; the research team and the pharmacy manager (who supervises all 7 pharmacies, see description in our prior paper [32]) will not be blinded to assignment because it would not be possible to do so, but individual pharmacists, pharmacy technicians, and others working in the control arms will not be aware that their pharmacies are serving as controls.

**Figure 1 figure1:**
[figure not shown]
Project flow diagram.

#### Participants and Procedures

This study will be conducted with an Indiana family-owned independent pharmacy system consisting of 8 pharmacies. The organization has been operational for over 120 years and predominantly operates in rural communities. Its pharmacies offer a variety of services including infusions, durable medical equipment, medication delivery, and cost containment. This organization reports continually seeking ways to expand its services to meet community needs.

The pharmacy manager has already agreed in principle that the organization sites will participate in this pilot cluster randomized trial. Data collected at the site level will be obtained from these entities, which are the only eligible pharmacies (n=7). Within each pharmacy, all pharmacists and pharmacy technicians will be asked to complete 2 questionnaires. These individuals will be asked to provide individual-level consent and will not be required to complete the questionnaires.

Data from individual staff members will be collected prior to the intervention (a 2-week window before the start date) and after the intervention (a 2-week window after the end date). Staff members who are hired after the intervention begins will be eligible to take the second survey (posttest) but not the first (pretest). Aggregated data (ie, counts) on naloxone dispensing from the pharmacies will be collected retrospectively (the 3 months prior to the intervention initiation) and then monthly for the 3-month duration of the intervention using the pharmacies’ record systems. Data on the distribution of additional items (no-cost naloxone and referral cards) will be obtained through staff member counts of products at predetermined monthly intervals (all items will be numbered to facilitate accuracy).

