#### Intervention Description

The development of this intervention and the decisions made during that process, including the recent changes that were informed by the single-site pilot study, are described in detail in a prior paper [32]. Therefore, we have prepared a structured table (see Table 1) outlining the sequential steps in the intervention and refer readers to our prior paper for additional detail.

**Table 1 table1:** Intervention components.

Intervention stage	Steps	Other notes
Introduction to study (prior to study start date)	Digital video (.mp4) describing the intervention (~5 minutes in length) is distributed to the pharmacy manager. Pharmacy manager disseminates the video. All staff members view the video. Lead pharmacists are asked to include the video in the orientation package for new pharmacists and pharmacy technicians and those who may have missed the initial meeting.	Each pharmacy has a regular, site-specific “all hands” meeting each month. In the pilot and feasibility study, this meeting was identified as the appropriate venue to disseminate intervention information.
Early implementation (prior to study start date)	Confirm with the managing pharmacist that all intervention pharmacies have viewed the video at the “all hands” staff meeting. Deliver a set of 30 doses of naloxone (presently, individually packaged Narcan nasal spray) to each pharmacy in numerically marked bags imprinted with “Not for Sale.” Deliver a set of 500 consecutively numbered harm reduction referral slips to each pharmacy (customized for each pharmacy location). Deliver sets of reminder post-it notes to pharmacies. Deliver the requested number of yard signs to each pharmacy (based on the number of routes of travel around the pharmacy). Ensure that pharmacy’s in-store television has access to the scrolling reminder text.	Digital copies of all of the visual materials described here (3, 4, and 5) are freely available in a prior publication [32].

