#### Secondary Outcomes

As noted previously, this study will collect, describe, and in some cases analyze secondary outcomes to facilitate the interpretation of the study findings. These data and analyses will be treated as exploratory.

We will produce a count of the referral cards distributed by each intervention pharmacy by manual inspection of the individually numbered cards provided to each pharmacy. In addition, using a pretest-posttest methodology, we will collect individual-level data from pharmacy staff members (pharmacists and pharmacy technicians). Measures collected prior to the intervention will include the following (see Multimedia Appendix 1 for a copy of each instrument):

Sociodemographic information (age, gender, race, ethnicity, and sexual identity);Information about current pharmacy practice experience;Comfort with multiple harm reduction practices, as used in our prior study to explore harm reduction latent classes [27]; andMeasures of stigmatizing beliefs about people who use drugs, which combine components of the 2019 Brief Opioid Stigma Scale by Yang et al [46] and work by author [name]’s interdisciplinary group of medication for opioid use disorder patients and providers, which is in review.

The postintervention survey will include the comfort and stigma items (above) as well as additional sets of items (see Multimedia Appendices 2-3):

Intervention acceptability (4 questions adapted from the Consolidated Framework for Implementation Research [33]);A set of questions targeted at implementation optimization validated by Livet et al [47]; andFour evaluative items developed by our team to potentially inform future work (eg, “If you could wave a magic wand, how would you improve the PharmNet intervention?”).

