#### Statistical Analyses

We will analyze the primary outcome using a generalized linear mixed model with a Poisson distribution to compare change over time of the number of naloxone doses dispensed between study arms. We will include fixed effects for group, time, and their interaction and a random effect for pharmacy ID to account for repeated measures within pharmacy.

We do not anticipate any missingness in the primary outcome because the data are objective measures and can be accessed retrospectively if needed. If missing data are present in the individual-level data (>5%), we will perform multiple imputation by chained equations to assess the degree to which missingness affects the results. If missing data meaningfully affect the findings, we will report the analyses with imputation. If individuals provide a survey at one time point but not another (eg, a pretest without a posttest or vice versa), we will analyze the data as unmatched in our mixed models.

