## Appendix

Multimedia Appendix 1 PharmNet baseline survey.

Multimedia Appendix 2 PharmNet postintervention survey (existing staff only).

Multimedia Appendix 3 PharmNet postintervention survey (new hires only).

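### Staff hired after launch enter the exploratory comfort and stigma pre-post models as posttest-only records, so turnover after allocation can be mixed with change among existing staff (minor, cheap to fix)

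*Protocol article*

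**What the plan says.** All statements are in the protocol article.

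- **Who is surveyed.** Participants and Procedures invites all pharmacists and technicians at each of the 7 pharmacies to both surveys. On later joiners it says: "Staff members who are hired after the intervention begins will be eligible to take the second survey (posttest) but not the first (pretest".
- **When.** The posttest is taken "after the intervention (a 2-week window after the end date", and the intervention lasts 3 months. No latest hire date or minimum time in post is given.
- **How one-survey staff are analysed.** Statistical Analyses covers people who gave a survey at one time point but not the other, in either direction, and says "we will analyze the data as unmatched in our mixed models". No analysis confined to staff employed at the pretest is named.
- **What is measured.** Secondary Outcomes says "The postintervention survey will include the comfort and stigma items (above) as well as additional sets of items". Comfort and stigma are thus measured twice; acceptability, implementation and evaluative items only at the posttest. The same section labels the secondary data and analyses exploratory.
- **How new hires are handled in the field.** The Appendix lists two posttest forms: "Multimedia Appendix 2 PharmNet postintervention survey (existing staff only") and "Multimedia Appendix 3 PharmNet postintervention survey (new hires only"). Table 1 says of the introductory video: "Lead pharmacists are asked to include the video in the orientation package for new pharmacists and pharmacy technicians".

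**The concern.** Analysing unmatched records is sound for a baseline employee who skipped one survey, because that person belongs to the group whose change is being estimated. A person hired after launch is in a different position. The pretest is closed to them by rule, they had no pre-intervention state at that pharmacy, and they joined after the pharmacies were allocated. The article's rule treats both kinds of record alike.

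If new hires differ from existing staff in comfort or stigma, for example because they trained more recently, the posttest mean moves even when no existing employee has changed. A reader would then take a change in the composition of the workforce for a change in attitudes. At stake is the reading of the staff-level results, which the article says are there to help interpret the study findings.

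**Working it through.** **The plan's own figures.** The article gives no figure on this point: no staff numbers, no turnover, no expected difference between new and existing staff. Its one design figure, a detectable Cohen d of 2.68 for 4 v 3 pharmacies, reproduces (a two-sample t-test with noncentral t gives 2.684) but concerns pharmacies and has no bearing here.

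**Inputs.**
- From the article: a 3-month intervention (about 13 weeks), a 2-week posttest window, new hires posttest-only, one-survey staff kept in the models.
- Assumed: new hires are a share f of posttest respondents, 10% to 30%. They differ from existing staff by delta = 0.5 to 0.8 SD. The within-person correlation between pretest and posttest is rho = 0.3 to 0.6.

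**Step 1: weight of new hires in the estimated change.** Take one arm with paired staff plus posttest-only new hires, and a model with a random intercept per person. The generalised least squares estimate is

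change = (1 - rho) x pooled posttest mean + rho x paired posttest mean - paired pretest mean.

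The pooled posttest mean equals the paired posttest mean + f x delta. The shift caused by new hires is therefore (1 - rho) x f x delta. This leaves out clustering by pharmacy and staff with a pretest only.

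**Step 2: shift within one arm.**
- Low: (1 - 0.6) x 0.10 x 0.5 = 0.02 SD.
- High: (1 - 0.3) x 0.30 x 0.8 = 0.168, about 0.17 SD.

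This applies to a pre-post reading of a single arm, without the control arm.

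**Step 3: bias between arms.** With common rho and delta, the bias in the arm-by-time contrast is (1 - rho) x (f in one arm - f in the other) x delta.
- Equal turnover: the difference in f is 0, so the bias is 0.
- 30% v 10%, low: 0.4 x 0.20 x 0.5 = 0.04 SD.
- 30% v 10%, high: 0.7 x 0.20 x 0.8 = 0.112, about 0.11 SD.

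The sign depends on which arm hires more and on the direction of delta.

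**Step 4: people hired after the end date.** If hires arrive evenly from launch to the close of the posttest window, the share hired after the intervention ended is 2 / (13 + 2) = 13%. As a share of all posttest respondents this is 0.10 x 0.133 = 1.3% to 0.30 x 0.133 = 4.0%.

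**Step 5: effect of the fix.** With only staff employed at the pretest in the comparison, f = 0 and the shift in Steps 2 and 3 is 0.

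**The case against.** The strongest reply is that surveying whoever staffs the site at each time is a recognised open-cohort approach in a cluster trial. Pharmacies are randomised, not staff; the trial is pragmatic; and a dedicated form shows that including joiners was deliberate. This stands. Surveying new hires is a legitimate choice, and the point is only that the stated model does not separate two quantities that a reader will want apart.

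A second reply is that both arms are surveyed, so equal turnover cancels, and the article gives no reason why a signage, referral-card and naloxone-supply programme would change hiring. This also stands, and it makes the expected bias small. It does not remove the point: with 4 v 3 pharmacies, chance alone could leave the arms with different shares of new hires, and a within-arm reading has no cancellation.

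Three stronger readings are tempting, and the documents do not support them.
- *That acceptability ratings are pooled over new and existing staff.* The unmatched-data rule concerns surveys given at one time point but not the other, so it bears on the repeated measures. No pooling is stated for the posttest-only items. New hires have their own form, whose content is not shown.
- *That new hires are unexposed.* Someone hired during the 3 months works under the running programme, and the video is meant to be part of orientation. Only people hired after the end date miss the active period, and they are few (Step 4).
- *That the trial's conclusion is at risk.* The rule in Next Steps turns on Hypothesis 1, which is naloxone dispensing from pharmacy records and numbered doses. Staff surveys do not enter it.

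**Conclusion.** The point holds as a minor, inexpensive improvement. As written, staff hired after launch, with no latest hire date, can enter the comfort and stigma models as posttest-only records, and the estimated change can mix turnover after allocation with change among existing staff. The between-arm bias is zero when the share of new hires and their difference from existing staff match by arm, and about 0.04 to 0.11 SD under a marked imbalance of 30% v 10%. The turnover shares, delta and rho are all assumptions, since the article supplies none of them. The affected outcomes are exploratory; the primary outcome and the decision on a larger trial are not affected.

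**What to change.** - **Statistical Analyses:** base the comfort and stigma pre-post comparison on staff employed at their pharmacy at the pretest, in its randomised arm, including those who completed only one of the two surveys. Report new hires, whom the separate form already identifies, separately and descriptively. Show the model that pools them with existing staff as a sensitivity analysis.
- **Participants and Procedures:** limit new-hire eligibility for the posttest to people hired before the intervention end date. The article offers no basis for a particular minimum number of weeks in post, so none is proposed.

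The cost is a few sentences of wording. The downside is slightly fewer posttest records in the main staff model. Answers from people hired during the intervention are still collected and reported; only the few hired after the end date are no longer surveyed.
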